## Materials and methods

### Study design and setting

This study adheres to the latest guidelines for reporting parallel-group randomized trials [18]. The University of Central Lancashire in the city of Preston in Lancashire, Northwest England, will serve as the location for the trial. In accordance with our previous trial, this research follows a 20-day parallel design, incorporating randomized allocation with a placebo control [16] (Figs 1-2). After screening for eligibility and enrolment, participants will then be randomized at the individual level, using a computer program (Random Allocation Software) undertaken by an independent researcher to either a peppermint or placebo group. A permuted block randomization process will be adopted to ensure equal allocation to each trial arm based on the required sample size. Participants and the data analyst will be unaware of the study-group assignments throughout data collection. Indices, pertinent to hypertension, as described in detail below, will be assessed at baseline and after 20-days (post-intervention). In agreement with previous trials involving hypertensive individuals, the primary outcome measure will be the between-group difference in systolic blood pressure from baseline to post-intervention [16,19]. Secondary outcome measures will be between-group differences in anthropometric, haematological, diastolic blood pressure/ resting heart rate, psychological wellbeing and sleep efficacy indices. All experimental visits will take place in the morning and be undertaken in a ≥ 10-hour fasted state. Participants will also be required to arrive hydrated and to avoid strenuous exercise, alcohol, and nutritional supplements 24 h and caffeine 12 h prior.

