### Sample size

Given the lack of randomized trial data in this population specifically for peppermint, a pragmatic a priori sample size calculation was undertaken based on our previous trial involving healthy individuals [16]. In this, we observed Cohen’s *d* = 0.81 for the primary outcome. Therefore, as we anticipate a larger effect of peppermint in individuals with pre and stage 1 hypertension, we pragmatically selected a Cohen’s *d* = 0.85. This effect size, combined with the directional nature of our hypotheses, meant that to achieve *α* = 5% and *β* = 0.80, a total sample size of 36 is necessary. To account for a 10% dropout rate, which was conservatively estimated based on our previous trial [16], we adjusted the total sample size to 40 participants.

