### Dietary intervention

After the conclusion of their baseline data collection session, participants will be provided with either pure peppermint oil (Piping Rock Health, UK) or placebo. Participants randomized to the peppermint arm will be required to consume 50 µ L of supplement diluted into 100 mL of water twice daily: once in the morning and again in the evening [16,17]. The placebo condition will involve the consumption of a peppermint flavoured cordial (Schweppes, Schweppes Geneva) in the same quantity and manner as the peppermint group. The placebo is the same colour as the peppermint supplement, without the presence of peppermint. To ensure effective blinding, identical opaque 15 mL dropper bottles without any labels, will be supplied to participants in both the placebo and peppermint trial groups, with the only difference being the solution, i.e., placebo or peppermint that they contain. This method of placebo preparation has been shown by previous analyses to provide an effective blinding strategy [16,21]. Additionally, all supplements will be prepared by an independent researcher to maintain blinding, ensuring that the trial researchers are also unaware of the participants’ allocations.

Throughout the study, the participants will be encouraged to maintain their habitual diet and exercise routines; and asked to refrain from consuming any other peppermint supplements. Participants will also be asked to keep a 4-day diet diary prior to the baseline assessment and before the follow-up examination at the end of the 20-day treatment period [19]. This will ensure that there are no differences in dietary patterns between groups and that participants have not made significant changes to their nutritional approach that could influence the study outcomes. For their post-intervention data collection session, all participants will be asked to return any un-used supplementation/ placebo to the laboratory in order to determine the % compliance in each group. Furthermore, in order to examine blinding efficacy, each participant will be asked to which trial arm that they felt that they had been allocated to at the conclusion of their post-intervention data collection session. Participants displaying any adverse events will be discontinued from the study at the earliest opportunity and in both groups loss to follow up will be monitored, as will be any adverse events.

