### Statistical analysis

Continuous experimental variables will be presented as mean values along with their corresponding standard deviations. To compare compliance levels between the trial arms, between-group linear mixed effects models will be utilized. In these models, group will be treated as a fixed factor, and random intercepts will be included for participants.

All analyses of the intervention-based data will follow an intention-to-treat approach. To determine the effects of the intervention on all of the outcome measures, differences in the changes from baseline to 20-days between the two trial arms will be examined using linear mixed-effects models with a group modelled as a fixed factor and random intercepts by participants adopted, employing the restricted maximum-likelihood method [16]. For linear mixed models, the mean difference between groups in changes from baseline to 20-days (*b*) and 95% confidence intervals of the difference will be presented. As the experimental questionnaires yield data that are predominantly ordinal in nature, the aforementioned effects of the intervention between trial arms will be examined using Mann-Whitney U tests. Effect sizes will be calculated for the changes from baseline to 20-days between the two groups, using Cohen’s d, in accordance with McGough & Faraone, [39]. Cohen’s *d* values will be interpreted as 0.2 = small, 0.5 = medium, and 0.8 = large [40]. The efficacy of blinding will be assessed using a one-way chi-square (*Χ*^2^) goodness-of-fit test [16]. Chi-square analyses will be calculated using Monte-Carlo simulation to determine probability values. All statistical analyses will be performed using SPSS v29 (IBM Inc., SPSS, Chicago, IL, USA), and statistical significance will be considered at a P ≤ 0.05 level.

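### The one-way chi-square test of blinding has no stated categories; applied to guessed arm it ignores allocation, and applied to pooled correctness it can mask one arm, so guesses should be reported by allocated arm.

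*Protocol article*

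**What the plan says.** In the Dietary intervention section, at the end of the post-intervention session, "each participant will be asked to which trial arm that they felt that they had been allocated to". The guess is therefore recorded for each participant who attends that visit.

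The Statistical analysis section then says: "The efficacy of blinding will be assessed using a one-way chi-square" goodness-of-fit test, with a citation to the group's previous trial. It adds that "Chi-square analyses will be calculated using Monte-Carlo simulation to determine probability values" and that "statistical significance will be considered at a P ≤ 0.05 level".

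The article does not say which categories the test compares or which proportions it expects. It mentions no table of guess against allocated arm and no summary by arm.

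Two design facts bear on the test. Permuted blocks are used to "ensure equal allocation to each trial arm". The Sample size section requires 36 participants, and to allow for dropout "we adjusted the total sample size to 40 participants".

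**The concern.** Blinding concerns the relation between what participants guess and what they received. A one-way goodness-of-fit test examines a single variable against fixed proportions. If that variable is the guess, the test cannot tell guesses that match allocation from guesses unrelated to it. With equal arms, participants who all know their treatment split their guesses evenly, which is the pattern the test treats as ideal. If the variable is correct versus incorrect, allocation does enter, but pooling the arms averages them.

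At stake is how far the blinding check can be relied on. It matters most for the self-completed sleep, anxiety, depression and wellbeing questionnaires, where expectation can act directly on the answer. It matters less for the primary outcome, which is read from an automated monitor.

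**Working it through.** **Inputs.** There are 20 per arm if all 40 randomised participants give a guess, and 18 per arm if the 36 in the Sample size section do (40 × 0.90 = 36). Allocation is 1:1. The article gives no figure for the blinding test itself, so there is none to reproduce. Expected proportions of 50:50 are assumed.

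**Formula.** For two categories with counts a and b against 50:50, chi-square = (a − b)² / (a + b) on 1 degree of freedom. Exact values below are two-sided binomial P values, which a Monte-Carlo P value approximates. Fisher's test is applied to the 2 × 2 table of allocated arm by guess.

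**Coding A: guessed arm (peppermint or placebo), pooled over arms.**

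| Scenario (correct guesses) | Guesses peppermint:placebo | Chi-square | P | Fisher P |
|---|---|---|---|---|
| 18/18 and 18/18 | 18:18 | 0²/36 = 0 | 1.0 | 2e-10 |
| Peppermint 20/20, placebo 14/20 | 20 + 6 = 26 : 14 | 12²/40 = 3.60 | 0.058 (exact 0.081) | 3e-6 |

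If each participant in arms of 20 guesses correctly with probability 0.8, the one-way test is non-significant with probability 0.99, and Fisher's test with probability 0.04.

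**Coding B: correct or incorrect, pooled over arms.**

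| Scenario (correct guesses) | Correct:incorrect | Chi-square | P |
|---|---|---|---|
| 18/18 and 18/18 | 36:0 | 36²/36 = 36 | 2e-9 (detected) |
| 15/18 and 8/18 | 23:13 | 10²/36 = 2.78 | 0.096 (exact 0.13) |

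In the second row the first arm alone has a blinding index of 2 × 15/18 − 1 = 0.67 (exact P = 0.0075), and the other has 2 × 8/18 − 1 = −0.11.

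**One arm fully unblinded, the other guessing at random.** The expected split is the same under both codings: 27:9 with 18 per arm (18²/36 = 9.0, P = 0.003) and 30:10 with 20 per arm (20²/40 = 10.0, P = 0.0016). The chance of a non-significant exact result is about 0.12 and 0.06 respectively, so this case is usually detected.

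**How much a non-significant P is worth.** If each participant in arms of 20 guesses correctly with probability 0.6, the result is non-significant with probability 0.97 under coding A, 0.79 under coding B and 0.86 with Fisher's test. At this sample size no version of the test gives much reassurance when it is non-significant.

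**Precision of per-arm reporting.** Near chance guessing, the approximate 95% half-width of the index is 2 × 1.96 × √(0.25/n): 0.46 for n = 18 and 0.44 for n = 20.

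**The case against.** The strongest reply is that the most serious failure depends on a coding the article never states. The test is cited to a previous trial that is not at hand, and a journal article condenses the full protocol. If the categories are correct and incorrect, allocation is built in and joint unblinding is found at once. A four-cell version (arm by guess) would also find it (P = 7.5e-8 with 18 per arm), although one-way does not naturally mean that. This stands, and it is why the point is conditional on the coding. It does not remove the point: guessed arm is the variable the article says is collected, and the pooled correctness coding has its own blind spot.

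It is also fair that a two-way P value alone is no cure. For 15/18 and 8/18 correct, the arm-by-guess table is 15/3 against 10/8 and Fisher's P is 0.15. Coding A would see 15 + 10 = 25 against 11 and flag it (14²/36 = 5.44, P = 0.020, exact 0.029). The estimates for each arm are what show the problem.

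A reader might infer three stronger things, which the document does not support:

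- **That the test generally misses a fully unblinded arm.** Beside a randomly guessing arm it usually does not, under either coding.
- **That blinding will fail because the cordial is taken** "in the same quantity and manner as the peppermint group". There are no sensory data. The placebo is described as flavoured and colour-matched, in identical opaque bottles, with earlier work cited for the method.
- **That the investigators will declare success from P > 0.05, offer no undecided answer, or show blood pressure results before asking for the guess.** The article says none of these things.

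**Conclusion.** The concern holds in conditional form. The stated method names a one-variable test for a question about two variables and leaves its categories open. With guessed arm against an assumed 50:50, complete unblinding of both equal arms gives P = 1.0, and 20/20 with 14/20 correct gives P = 0.058. With pooled correctness, joint unblinding is detected but 15/18 in one arm can be offset by 8/18 in the other (P = 0.096, exact 0.13).

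These figures assume 18 to 20 guesses per arm and two response categories. This is a supporting check: it changes no effect estimate and does not touch the primary analysis. It is still worth correcting, because on the plain reading the worst case gives the most reassuring result.

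**What to change.** Replace the one-way test with a cross-tabulation of guessed arm by allocated arm. For each arm, report the proportion guessing correctly, or a blinding index such as Bang's, with a 95% confidence interval. State the response categories. If a P value is kept, say that a non-significant result with about 36 to 40 participants will not be taken as evidence that blinding held.

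The cost is a change of analysis wording. Guess and allocation are both recorded, so the change also covers participants who have already finished, and the primary analysis of systolic blood pressure is unaffected. The drawback is imprecision: with 18 to 20 per arm the index carries roughly ±0.45 near chance guessing, so moderate unblinding can be neither confirmed nor excluded. The report should say so.

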### Safety reporting

The Sponsor’s Adverse Event Reporting Procedures shall be followed for reporting adverse events. The clinical co-investigator will be in charge of assessing the cause and severity of adverse events, as well as ensuring that appropriate action is done. Data on adverse events will be gathered from the start of any study-related procedure (i.e., upon acquisition of written consent). The participant’s final trial contact will mark the end of the adverse event reporting period.

Throughout the study, we will closely monitor and document both significant and non-serious adverse effects that may be associated with participation in the research or lead to withdrawal from the or study. Serious adverse events encompass any unfavourable medical event. In the event of any necessary modifications to the experimental protocol, we will promptly inform the study ethics committee for re-evaluation and approval, and the trial registry will be updated accordingly. During this period, data collection will be temporarily halted. Non-serious incidents, on the other hand, encompass medical occurrences that do not meet the criteria for serious adverse events.

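### Serious adverse events are defined so broadly that no adverse event can be classed as non-serious

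*Protocol article*

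**What the plan says.** All the relevant text is in the Safety reporting section of the protocol article.

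- Two classes are intended: "we will closely monitor and document both significant and non-serious adverse effects".
- The serious class is defined by one sentence: "Serious adverse events encompass any unfavourable medical event".
- The other class is the remainder: "Non-serious incidents, on the other hand, encompass medical occurrences that do not meet the criteria for serious adverse events".
- On procedure, the sponsor's "Adverse Event Reporting Procedures shall be followed for reporting adverse events".
- On assessment, "The clinical co-investigator will be in charge of assessing the cause and severity of adverse events".

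Elsewhere, the Dietary intervention section says that adverse events will be monitored in both groups. No other section of the article says what makes an event serious.

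**The concern.** The sentence gives the general meaning of an adverse event under the label of a serious one. A serious class only has a use if some adverse events fall outside it, and here none can. Anyone applying the text literally would class a mild, passing symptom as serious, and an event of real gravity would carry the same label.

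Staff might instead apply their own judgement or another document. The classification would then differ from the published definition, and a reader could not check it against the article.

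What is at stake is the serious/non-serious split and any statement that relies on it. The Introduction contrasts peppermint with drug treatments partly on adverse effects, so readers may well look for that split when the trial reports.

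**Working it through.** No arithmetic applies, because the article gives no figure on this point. The check is to read the sentences together and then look for anything that repairs them.

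**Step 1: the definitions.** Let U be all unfavourable medical events (the adverse events), S the serious class and N the non-serious class.
- The first definition places every member of U in S. This holds whether the verb is read as equating the two (S = U) or only as including one in the other (U within S).
- The second definition makes N the medical occurrences outside S.

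**Step 2: the consequence.** If all of U lies in S, and N lies outside S, then U and N have no member in common. By definition, 100% of adverse events are serious and 0% are non-serious, whatever the number or kind of events.

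**Step 3: is N strictly empty?** Not quite. It is worded in terms of medical occurrences, which is wider than unfavourable events, so a neutral or favourable occurrence could fall there. Such occurrences are not adverse events, so the non-serious adverse event class remains empty.

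**Step 4: conflict with the stated intent.** The section promises to document two kinds of adverse effect. It calls the first kind significant rather than serious. I read the two words as the same class, since the section goes on to define serious and non-serious as its pair. On that reading, the intent needs two classes and the definitions allow one.

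**Step 5: does other text repair it?**
- The remainder definition refers to criteria for serious events, but none are stated in the article.
- The reference to the sponsor's procedures concerns reporting. It does not say that they define seriousness or take precedence over the printed sentence.
- The clinical co-investigator is assigned cause and severity. Seriousness is not named.

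**Step 6: what does not depend on the definition.**
- Collection of events from consent to final contact.
- The assessment of cause and severity.
- The total number of events.
- The primary outcome (systolic blood pressure) and the sample size of 40.

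**The case against.** The strongest reply is that this is a condensation error. The section opens by requiring the sponsor's procedures to be followed, and it speaks of criteria as if they exist somewhere. A journal article may leave the list of criteria to a fuller document, and practice at the site may be sound.

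Part of that stands. The procedures are not shown, so misclassification is a risk of following the article and not something shown to have happened. But the article is not silent. It prints a definition, and that definition defeats its own classification. If the sponsor's procedures hold proper criteria, the article conflicts with them and still needs correcting.

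It can also be said that the error is on the cautious side, since a serious event would not be missed. That is right, and it limits the importance of the point. It does not make the split usable.

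A reader might go further and infer any of the following. The documents do not support them.
- *Published counts of serious events by arm will be wrong.* The article plans no such table.
- *Reports of serious events to the ethics committee will be confused.* In this section the committee appears only in connection with protocol modifications; the article describes no reports of serious events to it.
- *The safety conclusion becomes uninterpretable.* Safety is not among the stated objectives, hypotheses or outcomes. Events with their cause and severity would still be on record and could be re-sorted.
- *A particular number of events will be mislabelled.* The article gives no expected adverse event rate, so no count can be derived.

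**Conclusion.** The point holds as a wrong statement in the text. As written, every adverse event is serious and none can be non-serious, which contradicts the plan to document both classes. Any serious/non-serious split reported from this definition would be wrong.

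The effect is confined to that split. The finding rests on two assumptions: that the printed sentence is applied as it stands, and that nothing in the unseen sponsor procedures overrides it. If the second fails, what remains is a conflict between the article and the procedures, with the same remedy. It should be corrected because the correction is cheap and the label matters to readers; it does not threaten the trial's main result.

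**What to change.** Replace the sentence with explicit seriousness criteria, or cite the place in the sponsor's procedures where they are defined. Then state that all other untoward events are non-serious, so that the two definitions fit together. It would also help to use one term where the section now alternates between significant and serious. The content of the criteria should come from the sponsor's procedures, which are not available here.

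The Participants and recruitment section dates the start of data collection to January 2024 and anticipates that it will run until September 2025, so events may already have been logged, although nothing shows that any have. Check, while still blinded, that any recorded event is classified under the corrected definition.

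The cost is a one-sentence correction, notification to the ethics committee and a short re-check of recorded events. The sponsor should settle beforehand whether this counts as a modification to the experimental protocol. If it does, the section's own rule adds committee re-evaluation and approval, a registry update and a temporary halt to data collection.

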### Ethics and dissemination

This study has been granted ethical approval by the University of Central Lancashire Health Ethics Committee (HEALTH 01074) and has formally been registered as a trial (NCT05561543). When the data have been evaluated, participants who request to see a summary of the study results will be given that information. Publication in a peer-reviewed journal and presentation at both national and global scientific conferences will be the primary means of disseminating the study findings from this trial.

## Conclusions

The proposed placebo randomized controlled trial aims to investigate the effects of peppermint supplementation in individuals with pre and stage 1 hypertension. The study seeks to determine the effectiveness of a 20-day intervention involving twice-daily peppermint supplementation on various aspects of this disease modality. The primary objective of this trial is to assess the impact of the intervention on systolic blood pressure. Additionally, the study will utilize other health-related questionnaires to gather information on different aspects of hypertensive health including anthropometric, haematological, diastolic blood pressure/ resting heart rate, psychological wellbeing and sleep efficacy indices. The predicted outcomes of this trial suggest that peppermint supplementation will lead to significant improvements in systolic blood pressure compared to the placebo. Should the findings of this randomized controlled trial support these predictions, they would provide valuable and clinically significant information. Given the debilitating nature of hypertension, its associated healthcare costs, as well as the negative effects of this condition on quality of life and psychological well-being, the results could have practical implications for improving the management and treatment of early-stage hypertension using peppermint supplementation.
